#### Measures

Measures include the same background information, self-rate questions and self-evaluation scale of competence and the PBCT as used in Study 1. In addition, students’ therapy sessions will be recorded using the MyJYU AI transcript service, which automatically transcribes audio recordings into text. Text transcripts will be used as data to facilitate the analysis of session content.

Client participants complete background questionnaire information such as demographic variables (e.g., (options categorized, e.g., age group, gender, marital status, working status), expectations and attitudes toward the intervention provided by students (e.g., beliefs of usefulness, expectations of benefits, expectations of student therapist competence), and health-related demographic variables (options categorized, e.g., previous use of psychological support services, current use of medication for somatic or psychiatric conditions, current somatic health issues, self-evaluated current health).

Additionally, client participants in WP3 will complete several questionnaires to assess their situation before the intervention, during the intervention (after session 3) and after the intervention. Shorter versions were selected to minimize response fatigue, while multiple questionnaires were chosen to capture a range of psychological processes. Measuring various aspects helps address co-occurring indicators in the client’s situation and identify key psychological processes of change that could lead to better outcomes in process-based interventions. The aim is to measure both symptoms and processes to explore different psychological dimensions and therapeutic targets, providing a more comprehensive understanding and assessment of the client, while keeping the measures limited in length to avoid fatigue. The process-based assessment tool (PBAT; [6]) will be used to measure processes of change, outcome, compassion and therapeutic alliance, the Comprehensive assessment of Acceptance and Commitment Therapy Processes (CompACT-10 [12],) to measure psychological flexibility, The Acceptance & Action Questionnaire (AAQ-2 [3],) to measure experiential avoidance, and the Cognitive Fusion Questionnaire (CFQ-13 [11],) to measure cognitive processes and fusion with thoughts. The Depression Anxiety Stress Scales – Short Form (DASS21 [28],) will be used to measure levels of mood and stress-related difficulties, the Patient Health Questionnaire (PHQ-9 [25],) to measure levels of mood-related difficulties, the Generalized Anxiety Disorder scale (GAD-7 [38],) to measure levels of anxiety-related difficulties, while the Shirom-Melamed Burnout Measure short version (SMBM-6 [1],) and the Dimensions of Anger Reactions questionnaire (DAR-5 [9],) to measure experiences of burnout and experience of anger respectively. The Mental Health Continuum Short Form (MHC-SF [24],) will be used to measure wellbeing, the Adult State Hope Scale (ASHS [37],) to measure sense of hope, including their goal-directed motivation and ability to find strategies to achieve goals, the State Self-Compassion Scale (SSCS-L [32],) to measure self-compassion and its subcomponents, and the Brunnsviken Brief Quality of Life Scale (BBQ [29],) to measure life satisfaction across six-life areas. Finally, life quality and physical health will be measured with an ad-hoc 1-item VAS scale.

#### Procedure

Recruitment for Study 3 is conducted in two arms: a) student participants are recruited within the context of teaching offered at the department of psychology at JYU, and b) client participants are recruited via advertisements and announcements circulated via email lists for mental health providers, publicly in social media and in the calls for study participants published on the JYU website.

Students are invited to enroll in a specific study mode of a course focused on delivering psychological interventions. This course is part of mandatory studies for a master’s degree in psychology. The current study provides one of the alternative modes offered on the course. The course content does not differ from general teaching practices, apart from completing the measures and other research related tasks.

Client participants are invited to take part in the study using targeted calls for participants that are circulated among local mental health providers and private practitioners who may identify persons who might be interested to participate in the study. Client participation is also invited by open calls in the JYU website for calls for participants and by a notice on the website of the Psychotherapy Research and Teaching Clinic at JYU. In addition, social media notifications are sent out in online groups and communities for mental health professionals and posted on public social media accounts for the project. These recruitment methods are aimed at identifying possible participants who are motivated in participating in a psychological intervention, but who do not have acute need for professional evaluation and treatment. All client participants must meet the inclusion and exclusion criteria designed to ensure client participants are fully aware that the interventions are provided by students practicing the provision of interventions and that participation does not substitute psychological treatment in situations where an individual feels they are in need of professional help. The self-report-based suitability assessment is accompanied by careful review of self-report scales of the level of psychological ill-being that all participants fulfill before initiating the interventions. In case a client participant reports severe symptoms that indicate the need for a professional evaluation and treatment planning, the participant will be excluded from the study and instructed to contact regional mental health services. To enroll in the study, participants respond to the initial enrollment survey that includes eligibility criteria and providing informed consent if eligibility criteria are met. After obtaining a consent, the research team view participants’ information and assign participants to student therapists. Students contact clients using their university email to schedule the first meeting that consist of an initial interview. Students are instructed to use email only to set up the initial meeting time and to provide standardized instructions on next steps. A research assistant is hired to manage all further communication, including handling cancellations. After contacting the client and making sure that consent is obtained, students schedule a time for the first session.

Before starting each session, students log in their MyJYU application to audio record the sessions, which are safely stored on a secure JYU database. Clients are asked to complete a survey containing questionnaires on psychological well-being, flexibility, symptomatology, and daily functioning after giving consent and during the week before their session (more details in measurement section). They are asked to complete the same survey again after the third session of the six-session intervention and at the end of the intervention.

Students conduct the PBCT and other measures at four time-points: one month before the training begins, immediately before the training, after training, and after the interventions have been delivered. This allows for the evaluation of the test–retest properties of the PBCT, and for establishing a baseline of variation in competence in the absence of training. Client participants are asked to complete outcome and process questionnaires at three time-points: recruitment, after session three, and after the intervention.

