To date, the validity of many competence measures has not been systematically evaluated and reported. The problem may have been exacerbated by the current requirement to report an evaluation of therapists’ adherence and competence in randomized controlled trials as part of research integrity reporting. The focus has been on validating the design of the intervention under examination in a given trial, instead of the sensitivity of the method used for evaluating competence. This may have yielded overly optimistic ratings of competence. For example, some studies have reported “very good” or “excellent” competence for 92% of novice therapists [10]. Another common issue is the considerable variation in the trial-specific conceptualization and rating procedures. As research on competence-outcome effects is arguably lacking, the comparability of results is a crucial consideration. Variation in competence evaluation stemming from confounding factors, such as alliance or the nature and severity of the participant’s symptoms, can also influence or obscure the relationship between competence and outcomes [40]. This may be a severe shortcoming, as it directly undermines the importance of advanced training for mental health professionals. Overall, previous null results of the association between competence and outcome may reflect methodological issues, such as poor conceptualization, rating competence in settings that include multiple sources of variation, and insufficient attention to the sensitivity of existing competence measures. This calls for revisiting the research on therapist competence with adequate precision. A process-based therapy approach, which focuses on core clinical competencies in targeting empirically established change processes, can guide the development of novel competence evaluation methods.

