The current research will progress in three subsequent sub-studies that build upon one another. The study aims to meet the following research goals in these three sub-studies:*The aim of Study 1* is to develop the PBCT and validate sensitivity to therapist experience. Research questions under Study 1 are: a) Does the PBCT show sensitivity to previous experience and training? b) Are therapists’ formal and informal training, work-related variables (e.g., work settings), and self-reported attributes related to competence and confidence associated with performance in the PBCT? This validation stage will be deemed successful if performance in the PBCT is associated with the level of training.*The aim of Study 2* is to continue the validation of the PBCT by ensuring responsiveness to further training. The second validation stage will be deemed successful if performance in the PBCT is improved after additional training for master’s students of psychology and psychotherapist trainees. In addition, the association between therapist characteristics and competence development are analyzed. Research questions under Study 2 are: a) Does the PBCT detect increases in competence during one year of psychotherapist training or brief psychology master’s program training? b) Are therapists’ formal and informal training, work-related variables (e.g., work settings), and self-reported attributes related to competence and confidence associated with performance in the PBCT?*The aim of Study 3* is to provide evidence of the importance of therapist competence for treatment outcomes in a brief intervention for enhancing mood and wellbeing delivered by novice therapists. In addition, competence development during brief training and intervention delivery is examined. Research questions under Study 3 are: a) Does the PBCT detect increases in novice therapists' competence after brief training or during the intervention? b) Is competence associated with the outcome of a brief intervention for mood problems provided by novice therapists? c) Can individual differences in the initial level of competence and changes in competence during training or delivery of the intervention be identified and modeled to improve training practices?

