#### Analysis

The analyses for Study 3 will focus on the relationship between treatment outcomes and competence levels using multiple regression analyses, while also examining within-group changes in competence among students during baseline, training, and intervention measures. For Study 3, a minimum sample size for client participants was 118 for multiple regression analysis with up to ten predictors in the model to examine multiple change predictors. The anticipated effect size (f2) was set to 0.15, and the desired power level was set to 0.80. To anticipate drop-out, the sample size of client participants was set to 140 (70 student therapists with two clients each).

The overall design of the studies is illustrated in Fig. 1 below.

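### Study 3 lets the research team assign clients to students after viewing client information, with no random or masked rule, so case difficulty could become linked to competence

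*Protocol article*

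**What the plan says.** The Study 3 Procedure describes the order of events for clients. An enrolment survey covers eligibility and consent; after consent, "the research team view participants’ information and assign participants to student therapists". The assigned student then makes contact to arrange the first meeting. No random, sequential or availability-based rule is given, and nothing is said about what the assigners know of the students. The same section mentions a "careful review of self-report scales of the level of psychological ill-being that all participants fulfill before initiating the interventions", which it ties to excluding clients with severe symptoms.

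Students complete the PBCT at four points: "one month before the training begins, immediately before the training, after training, and after the interventions have been delivered". Three of these precede the intervention.

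The research question affected is Study 3, question b: "Is competence associated with the outcome of a brief intervention for mood problems provided by novice therapists". The Study 3 Analysis section addresses it by examining "the relationship between treatment outcomes and competence levels using multiple regression analyses", sized for "multiple regression analysis with up to ten predictors in the model". The predictors are not named.

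**The concern.** Study 3 has no control arm. Question b rests on an observational regression of client outcome on therapist competence, so who treats whom decides whether the coefficient can be read as an effect of competence. If assigners send more difficult clients to students who seem stronger, competence becomes correlated with poor prognosis, and a real benefit shrinks or reverses. If they send easier clients to stronger students, the association is inflated. Either pattern would damage the inference Study 3 was set up to make.

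Measuring competence with a standardised video task, as the plan does, keeps client difficulty out of the competence score. It does not prevent difficulty from becoming correlated with the score through assignment.

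**Working it through.** **1. The plan's own figure.** Inputs from the Study 3 Analysis section: 10 predictors, f² = 0.15, power 0.80. Alpha is not stated; 0.05 is assumed. The overall F test has noncentrality λ = f² × N and degrees of freedom 10 and N − 11. The smallest N with power of at least 0.80 is 118 (power 0.801), as stated. The planned 140 clients (70 students × 2) give 0.883 and allow 1 − 118/140 = 15.7% drop-out. Nothing here disputes the sample size.

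**2. Matching on difficulty that the scales do not capture.** Assumed inputs, not in the article: correlation of competence with unmeasured difficulty 0.2 to 0.3; effect of difficulty on outcome 0.3 to 0.5 SD per SD. To a close approximation, bias = correlation × effect:

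- 0.2 × 0.3 = 0.06
- 0.2 × 0.5 = 0.10
- 0.3 × 0.5 = 0.15

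For scale, the test of one coefficient in a 10-predictor model at N = 118 has power 0.80 at a partial correlation of 0.252. Treating the standardised coefficient as roughly a partial correlation, a bias of 0.10 toward the null would turn 0.25 into 0.15. Power at 0.15 is 0.37 with 118 clients and 0.43 with all 140.

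**3. Matching on measured severity.** Assumed inputs: severity-outcome slope g = 0.5 SD, reliability of the baseline score 0.8, within-therapist correlation 0.05, and ρ = correlation of client severity with student competence created by assignment. The simulation used 70 students with two clients each, 1,500 runs and cluster-robust regression. The outcome is scored so that higher is worse, and harder cases go to stronger students.

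| True slope | ρ | Unadjusted slope | Rejection rate | Adjusted slope | Rejection rate |
|---|---|---|---|---|---|
| 0 | 0 | 0.00 | 6% | 0.00 | 6% |
| 0 | 0.2 | 0.10 | 23% | 0.02 | 6% |
| 0 | 0.4 | 0.20 | 67% | 0.05 | 10% |
| −0.20 | 0 | −0.20 | 67% | −0.20 | 74% |
| −0.20 | 0.2 | −0.10 | 25% | −0.18 | 65% |
| −0.20 | 0.4 | 0.00 | 7% | −0.15 | 49% |

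A closed form agrees. Unadjusted bias is gρ: 0.5 × 0.2 = 0.10 and 0.5 × 0.4 = 0.20. Bias left after adjustment is gρ(1 − 0.8)/(1 − 0.8ρ²): 0.020/0.968 = 0.021 at ρ = 0.2, and 0.040/0.872 = 0.046 at ρ = 0.4. Adjustment removes roughly four fifths of the bias in this scenario. It does not reduce the bias in step 2, which by definition concerns what the scales miss.

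**The case against.** A reader might infer that the assigners also train the students, hold their PBCT scores and match on ability. The article says none of this. It does not name the trainers, it describes the PBCT as an online task, and only access to client information is stated. A link between competence and difficulty needs assigners who know something of both.

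A reader might also take the Background as conceding the point, because it says that confounders such as symptom severity "can also influence or obscure the relationship between competence and outcomes". That sentence concerns competence ratings contaminated by client characteristics. It is not about how cases are allocated, and the plan answers it by measuring competence outside the clinic. Nor does the text support a claim that the bias most likely runs toward the null; the direction is open.

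Other objections have weight. It is unclear what information is viewed: the enrolment survey is described as covering eligibility and consent, and the timing of the full questionnaire battery relative to assignment is ambiguous. Viewing may serve eligibility checks or logistics. Severe and functionally impairing cases are excluded, which narrows the range of difficulty. Many symptom and process scales are collected at baseline and up to ten predictors are allowed, so adjustment is feasible; a condensed article may leave the covariate list to the analysis plan. The Discussion accepts that variation in client severity may affect interpretation of Study 3, although it attributes this to self-reported eligibility.

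These points reduce the likely size and certainty of the problem. They do not supply an allocation rule, and regression cannot adjust for a judgement that was never recorded.

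**Conclusion.** The concern holds as a risk that the stated procedure permits, not as a demonstrated error. Assignment follows the viewing of client information, with no random rule and no masking to student competence, and students will have been taught and tested before they treat anyone. The competence-outcome coefficient is therefore open to confounding by assignment, of unknown direction and size.

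Under the assumptions shown, the bias is about 0.02 to 0.05 after baseline adjustment if matching follows measured severity, and 0.06 to 0.15 if it follows unmeasured difficulty. The upper range requires a correlation of 0.2 to 0.3 with difficulty missed by all the baseline scales, which is demanding. If assignment is in practice unrelated to competence, there is no bias from this source. The sample-size figure is unaffected.

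**What to change.** Within each of the three waves, allocate eligible clients to available students by a computer-generated random list, two clients per student, run by someone without access to PBCT scores. The research assistant already planned for client communication could do this if kept apart from those scores. Permit departures only for scheduling, a conflict of interest (for example, a client known to the student) or a documented safety concern, and log each one. Include baseline severity as a covariate in the competence-outcome regression.

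The cost is one list per wave, plus the loss of discretionary matching and some scheduling flexibility. Eligibility rules, training, supervision and sample size stay as they are. The rule has to be set before clients are assigned, because analysis cannot fully repair discretionary assignment afterwards.

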#### Analysis

The analyses for Study 3 will focus on the relationship between treatment outcomes and competence levels using multiple regression analyses, while also examining within-group changes in competence among students during baseline, training, and intervention measures. For Study 3, a minimum sample size for client participants was 118 for multiple regression analysis with up to ten predictors in the model to examine multiple change predictors. The anticipated effect size (f2) was set to 0.15, and the desired power level was set to 0.80. To anticipate drop-out, the sample size of client participants was set to 140 (70 student therapists with two clients each).

The overall design of the studies is illustrated in Fig. 1 below.

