#### Design and setting of the study

Master’s level psychology students will receive a brief training on process-based CBT training, after which they deliver a short intervention to clients. Master’s level psychology students receive three days of training on a) building a functional case conceptualization to identify individual treatment targets, and b) using process-based CBT processes of therapeutic change. The training and provision of interventions are built in the mandatory studies offered to students completing a master’s degree in psychology. This novel training and related interventions serve as one of several modes of study for the students. Weekly supervision and peer-supervision are included in the curriculum for this mode of study on the course.

Second, the students will deliver the six-session intervention to two client participants. Interventions will be delivered in three waves. Students will receive weekly supervision from clinical psychologists and psychotherapist and attend weekly peer-supervision.

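### Study 3: the planned regression and its 118-client minimum make no allowance for clients being paired within 70 student therapists, so precision for competence and the stated power are modestly overstated

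*Protocol article*

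**What the plan says.** The model is named in the protocol article under Study 3, Analysis: "The analyses for Study 3 will focus on the relationship between treatment outcomes and competence levels using multiple regression analyses". The same paragraph gives the sample size: "a minimum sample size for client participants was 118 for multiple regression analysis with up to ten predictors in the model". It adds: "The anticipated effect size (f2) was set to 0.15, and the desired power level was set to 0.80". Allowing for drop-out, "the sample size of client participants was set to 140 (70 student therapists with two clients each". No significance level and no drop-out rate are given.

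Study 3, Design and setting of the study, describes the nesting: "the students will deliver the six-session intervention to two client participants. Interventions will be delivered in three waves". Study 3, Procedure, shows who is measured for competence: "Students conduct the PBCT and other measures at four time-points". The process-based competence task (PBCT) score therefore belongs to the student, and at any one time-point both clients of that student carry the same value.

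The regression serves Study 3 research question b (Research objectives and tasks), the association between competence and client outcome. The article mentions no ICC, design effect, multilevel model, cluster-robust standard error or aggregation to therapist level.

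**The concern.** The competence-outcome question compares therapists. It can draw on at most 70 competence values, although there are 140 client outcomes. If two clients of one therapist tend to fare alike for reasons the model does not capture, the second client adds less information on competence than an independent client would. Ordinary regression ignores this. Its confidence interval for competence is then too narrow and its p-value too small, and a sample size worked out on independent clients promises more power than a valid test delivers.

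The direction of the error matters here. The Background attributes earlier null findings on competence partly to weak methods, and Study 3 is meant to supply better evidence. An analysis that leans towards a positive competence finding would be an easy target for criticism.

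**Working it through.** **Inputs.** From Study 3, Analysis: 118 clients, ten predictors, f2 = 0.15, power 0.80, 140 enrolled as 70 × 2. Assumed: alpha 0.05 (not stated) and a residual therapist ICC of 0.05 to 0.20 (not stated). Residual means after competence and the other predictors are in the model.

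**1. Reproducing 118.** Overall F test of R² = 0 with numerator df 10, denominator df N − 11, noncentrality f2 × N and independent observations:
- N = 117: power 0.797
- N = 118: power 0.801

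So 118 is the smallest N that reaches 0.80. Nothing in it allows for pairing. The 0.80 belongs to the overall test of ten predictors. A test of one coefficient at f2 = 0.15 would need only 55.

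**2. Standard error for competence.** For a predictor constant within intact pairs, the design effect is 1 + (2 − 1) × ICC = 1 + ICC. The true standard error is about √(1 + ICC) times the ordinary one:
- ICC 0.05: √1.05 = 1.025
- ICC 0.10: √1.10 = 1.049
- ICC 0.20: √1.20 = 1.095

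**3. False-positive rate.** Intact pairs, closed form, 2 × [1 − Φ(1.96/√(1 + ICC))]: 5.6%, 6.2% and 7.4%. Simulation with 70 intact pairs and ten predictors gives 5.2%, 6.0% and 7.3%.

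If drop-out hits clients independently, retention is 118/140 = 0.843. Expected intact pairs are 70 × 0.843² ≈ 50, and single clients 70 × 2 × 0.843 × 0.157 ≈ 18 to 19, from about 68 therapists. The design effect eases to about 1 + 0.84 × ICC. The closed form then gives 5.5%, 6.0% and 7.0%. A simulation with independent drop-out gave about 5.3%, 6.3% and 7.5%. All these results agree on a small excess over 5%.

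**4. Power once pairing is respected.** Replace N by N/(1 + ICC). This is a worst case, because it treats all ten predictors as therapist-level and all pairs as intact.

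| ICC | 118/(1+ICC) | Overall power, 118 analysed | Overall power, 140 analysed | Competence alone, f2 = 0.15, 118 | Competence alone, f2 = 0.05 (assumed), 118 |
|---|---|---|---|---|---|
| 0 | 118.0 | 0.801 | 0.883 | 0.986 | 0.673 |
| 0.05 | 112.4 | 0.775 | 0.862 | 0.982 | 0.651 |
| 0.10 | 107.3 | 0.748 | 0.840 | 0.978 | 0.630 |
| 0.20 | 98.3 | 0.697 | 0.795 | 0.967 | 0.592 |

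With all 140 analysed, 0.80 is held while 140/(1 + ICC) ≥ 118, that is ICC ≤ 140/118 − 1 ≈ 0.186.

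**5. What restoring 0.80 would take in the worst case.** 118 × (1 + ICC) gives 124, 130 and 142 analysed clients. At the same retention, 140 × (1 + ICC) gives 147, 154 and 168 enrolled.

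**The case against.** **The article is condensed.** It never says that clients are treated as independent, and a full analysis plan could name a random intercept or clustered errors. That stands as far as wording goes: a reader might infer that the plan asserts independence, and it does not. But the article does fix a model and a sample-size basis, and 118 follows exactly from independent clients. A later plan could repair the model. It would not make 118 the right minimum for paired clients.

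**No power is claimed for competence.** This stands. A reader might infer that the 0.80 is the power for the competence association and that pairing undermines it. The documents do not support that. The 0.80 is for the ten-predictor test, and at the stated f2 a single competence coefficient keeps power of 0.967 at ICC 0.20.

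**The effect is small and the ICC is assumed.** This also stands. Pairs cap the design effect at 1.20 over the assumed range. The ICC that counts is residual, so the expectation that competence explains outcome does not by itself imply a positive value.

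**The power loss is an upper bound.** This stands too. Client-level predictors that vary within a pair, such as the baseline score, do not carry the full design effect, and drop-out will break some pairs.

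A reader might also infer further clustering by supervisor or wave. The article does not say how supervisors or waves are allocated to a student's two clients, so nothing can be concluded on that.

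**Conclusion.** The point holds in a limited form. The stated model and the stated minimum of 118 do not match the nested design described in the same paragraph. For any positive residual therapist ICC, the ordinary standard error for competence is too small and the stated power too high.

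The size is modest: false-positive rates stay within a few points of 5%, and power falls materially short of 0.80 only if the analysed number drops to about 118. This rests on an assumed ICC of 0.05 to 0.20 and alpha of 0.05. The documents do not support calling Study 3 invalid or its competence test underpowered at the stated effect size. If the true competence effect were nearer f2 = 0.05, power would be only 0.673 even without clustering. That is a separate reason to state power for this coefficient.

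**What to change.** For Study 3 research question b, replace plain multiple regression with a model of the post-intervention score that has the client's baseline score as covariate and a random intercept for student therapist. Use small-sample degrees of freedom (Kenward-Roger or Satterthwaite) for the competence coefficient. Therapist-clustered standard errors are an acceptable alternative.

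If the session-3 score is also used as an outcome, add a client-level random effect or a residual covariance for the repeated scores, and a competence-by-time term. Baseline should then remain a covariate only and not also enter as an outcome.

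State alpha and an explicit ICC range, such as 0.05 to 0.20, and give power over that range for the competence coefficient as well as for the overall test. If 118/(1 + ICC) is used, label it as a worst-case bound.

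Cost: a few sentences of analysis wording and a slightly less favourable stated power. No extra participants or data are needed, provided the lower power is accepted. The larger enrolment figures in the working arise only if 0.80 must be kept in the worst case at the same drop-out. The change should be made before outcome data are analysed.
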